On March 24, 2017, the use of nivolumab, an immune checkpoint inhibitor for patients with recurrent or metastatic head and neck cancer, was approved for insurance coverage in Japan. A few drugs are available to treat recurrent or metastatic head and neck cancers, and there are no established treatments for patients suffering from this condition; therefore, this drug is expected to serve as a new treatment option. The international Phase III trial (Checkmate-141 study) of nivolumab revealed significant OS prolongation in patients with platinum-resistant recurrent or metastatic head and neck cancer over the control arm of anticancer drugs and cetuximab. As mentioned above, FPE is the standard of care for recurrent and metastatic head and neck cancer. Still, it can further prolong survival and improve the quality of life for patients with poor prognosis. However, because the Checkmate 141 study included patients whose disease progressed within 6 months of completion of platinum-based chemotherapy, there is insufficient evidence in patients whose disease progressed after 6 months of completion of platinum-based chemotherapy.

2. Objectives

The purpose of this study is to evaluate the effects of nivolumab in patients with relapse or metastases 6 months after the completion of platinum-based chemotherapy.

3. Eligible patients

Expected number of patients: 50

(1) Inclusion criteria

Patients who met all the following criteria were included in this study:

1) Patients manifesting R/M-SCCHN six months after completing platinum-based chemotherapy

2) Primary site: the maxillary sinus, oral cavity, nasopharynx, oropharynx, hypopharynx, or larynx

3) Age 20-75 years

4) Eastern Cooperative Oncology Group performance-status (ECOG PS) score 0-1

5) Adequate organ functions defined as indicated below before registration in 14 days

(1) White Blood Cell ≧ 3,500 /mm3, White Blood Cell ≦ 12,000 /mm3

(2) neutrophil ≧ 2,000 /mm3

(3) Platelet ≧ 100,000 /mm3

(4) Hemoglobin ≧ 9.0 g/ dL

(5) Total bilirubin ≦ 1.5 mg/dL

(6) aspartate aminotransferase, alanine aminotransferase ≧ 100 IU/L

(7) Creatinine < 1.2 mg/dL

6) Written informed consent

(2) Exclusion criteria

Patients who met any of the following conditions were excluded from this study:

1) Patients with a history of severe drug allergy of nivolumab and similar drugs.

2) Patients with symptomatic brain metastasis and meningeal metastasis.

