3) Histologically proven primary unknown squamous cell carcinoma, salivary gland cancer, non-squamous cell cancer.

4) Patients with symptomatic autoimmune disease or history of autoimmune disease.

5) Patients with infection.

6) Patients with gastrointestinal disease (intestinal paralysis, bowel obstruction)

7) Patients with interstitial pneumonia or pulmonary fibrosis.

8) Uncontrolled diabetes.

9) Uncontrolled heart disorder.

10) Sever liver damage.

11) Patients with diarrhea.

12) Pregnant or lactating women or women with childbearing potential.

13) Men expecting partner's pregnancy.

14) Inadequate physical condition, as diagnosed by the attending physician

(3) Evidence for deciding the number of cases

This study is a single-arm phase II trial. The rate of recurrent or metastatic head and neck cancers at our institution is approximately 4 cases per month. Only 30% to 40% of the patients met the selection criteria and were eligible for enrollment. The study enrollment period is set at 2 years, and it is estimated that we will be able to enroll nearly 50 patients.

4. Material and Method

(1) Type and design

This is a prospective, interventional study in which nivolumab will be administered to subjects to evaluate treatment effects. It is an invasive study due to drug administration.

(2) Method

1) Patient enrollment

Patient enrollment will be determined by the principal investigator and sub-investigators.

2) Enrollment procedures

Confirm that eligible patients meet all eligibility criteria and none of the exclusion criteria, complete the Enrollment Eligibility Confirmation Form, and deliver it to the principal investigator. The principal investigator will review the information presented in the Enrollment Eligibility Confirmation Form and issue a registration number.

3) Treatment plan and treatment change criteria

Within 4 weeks of enrollment completion, treatment as per the protocol will be initiated under the direction of the principal investigator.

4) Protocol treatment

Nivolumab is administered at a single dose of 3 mg/kg (body weight) IV at 2-week intervals, which continues from the protocol initiation date until treatment is discontinued due to disease progression, unacceptable toxicity, other reasons.

5) Nivolumab discontinuation criteria

Discontinue nivolumab in the event of an adverse event (e.g., shock, anaphylactoid symptoms, etc.) determined to be attributable to this drug or in the event of a patient refusal.

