6) Withdrawal criteria and resumption criteria

At the initiation of nivolumab treatment (after the pre-course withdrawal period) or at any time during treatment, treatment should be continued after confirming that various laboratory tests have met the dosage criteria. If the dosage criteria are not met, the drug should be withdrawn and resumed according to the following criteria.

7) Criteria for drug withdrawal

If any of the following withdrawal criteria are met during treatment, treatment should be discontinued immediately, and treatment should be resumed while waiting for the patient's recovery to reach or exceed the withdrawal criteria.

In cases where the baseline is close to the withdrawal criteria, the investigator/assigned physician will decide on whether to discontinue treatment at the time the withdrawal criteria are violated.

| Inspection item | | Criteria for drug withdrawal | |
| --- | --- | --- | --- |
| Criteria for drug withdrawalBlood toxicity | White blood cell | < | 3,000 /mm3 |
| Neutrophil | < | 1,500 /mm3 |
| Platelet | < | 100,000 /mm3 |
| Hemoglobin | < | 9.0 g/ dL |
| Non-blood toxicity | Total bilirubin | ≧ | 2.0 mg/dL |
| Aspartate aminotransferase | ≧ | 100 IU/L |
| Alanine aminotransferase | ≧ | 100 IU/L |
| Creatinine | ≧ | 1.2 mg/dL |
| Other adverse events | ≧ | Grade2 |

8) Criteria for resuming administration

In the case of nivolumab administration, the following "Resumption Criteria" should be met before initiating nivolumab administration. The dose at the resumption of nivolumab administration is determined after confirming that the dose reduction criteria have been met.

If the withdrawal period for adverse events exceeds 28 days, the treatment is discontinued in this patient.

| Inspection item | | Criteria for resuming administration | |
| --- | --- | --- | --- |
| Blood toxicity | White blood cells | ≧ | 3,000 /mm3 |
| Neutrophil | ≧ | 1,500 /mm3 |
| Platelet | ≧ | 100,000 /mm3 |
| Hemoglobin | ≧ | 9.0 g/ dL |
| Non-blood toxicity | Total bilirubin | < | 2.0 mg/dL |
| Aspartate aminotransferase | < | 100 IU/L |
| Alanine aminotransferase | < | 100 IU/L |
| Creatinine | < | 1.2 mg/dL |
| Other adverse events | < | Grade1 |

9) Drug information

The following is a summary of the drug used in this study. Please refer to the most recent package insert for the drug for further information.

Nivolumab:

Generic name: Nivolumab

Product Name: Opdivo

[Contraindication]

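### Inclusion criterion 5(6) has its inequality reversed: it admits only AST/ALT of 100 IU/L or more, the same range at which the protocol stops nivolumab

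*Protocol*

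**What the plan says.** Protocol section 3(1) requires every inclusion criterion to be met. Item 5 is introduced as "Adequate organ functions defined as indicated below before registration in 14 days", and its sixth line reads "6) aspartate aminotransferase, alanine aminotransferase ≧ 100 IU/L". The bilirubin line just above it is an upper limit, "5) Total bilirubin ≦ 1.5 mg/dL", and the creatinine line just below it is also an upper limit (< 1.2 mg/dL).

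The dosing rules point the other way:

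- Section 4(2)7), criteria for drug withdrawal: "Aspartate aminotransferase | ≧ | 100 IU/L", with the same limit for ALT.
- Section 4(2)8), criteria for resuming administration: "Aspartate aminotransferase | < | 100 IU/L", with the same limit for ALT. The text above this table makes these criteria a condition for initiating nivolumab as well as for restarting it. Section 4(2)6) likewise applies the dosage criteria at the start of treatment.

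The eligibility list is a working checklist. Section 4(2)2) tells staff to "Confirm that eligible patients meet all eligibility criteria and none of the exclusion criteria" and to complete a confirmation form, which the principal investigator reviews before issuing a registration number.

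**The concern.** A minimum AST and ALT of 100 IU/L cannot define adequate liver function. Read literally, the criterion turns away patients with normal transaminases and admits those whose values already call for withholding the drug.

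Two things are at stake. First, the protocol has no correct written AST/ALT limit for entry, so the intended population is misdescribed on this point. Second, the twice-yearly monitoring in section 21 lists ineligible and possibly ineligible cases. If 5(6) were applied as printed, every patient with AST or ALT below 100 IU/L would be flagged, and eligibility could not be judged from the text alone.

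**Working it through.** No sample size, power or error rate is involved. The check compares each entry limit (section 3(1), item 5) with the withdrawal limit (section 4(2)7)) and the start/resumption limit (section 4(2)8)).

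| Item | Entry | Withdraw | Start/resume | Entry and withdrawal overlap? |
| --- | --- | --- | --- | --- |
| WBC (/mm3) | 3,500 to 12,000 | < 3,000 | ≧ 3,000 | None |
| Neutrophils (/mm3) | ≧ 2,000 | < 1,500 | ≧ 1,500 | None |
| Platelets (/mm3) | ≧ 100,000 | < 100,000 | ≧ 100,000 | None |
| Haemoglobin (g/dL) | ≧ 9.0 | < 9.0 | ≧ 9.0 | None |
| Total bilirubin (mg/dL) | ≦ 1.5 | ≧ 2.0 | < 2.0 | None |
| Creatinine (mg/dL) | < 1.2 | ≧ 1.2 | < 1.2 | None |
| AST (IU/L) | ≧ 100 | ≧ 100 | < 100 | Complete |
| ALT (IU/L) | ≧ 100 | ≧ 100 | < 100 | Complete |

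**Ranges.** For AST and ALT the entry range is [100, ∞), the withdrawal range is [100, ∞) and the start range is [0, 100). Entry equals withdrawal, and entry and start share no value. Six of the eight items are coherent. The two that are not both come from the single line 5(6).

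**Could one patient still meet both rules?** Only over time, because the rules act on different dates. The screening sample may be up to 14 days before registration. For the first dose, section 4(2)3) says "Within 4 weeks of enrollment completion, treatment as per the protocol will be initiated". If registration and enrolment completion fall on the same day (an assumption), the longest gap is 14 + 28 = 42 days. Both AST and ALT would have to fall from 100 or more to below 100 within that gap.

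**Is it a lost symbol?** Unlikely. The same list prints ≦ correctly for the WBC upper limit and for bilirubin, and nothing elsewhere in the protocol corrects line (6).

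**Candidate corrections.**

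- With < 100, entry equals the start range and has no overlap with withdrawal.
- With ≦ 100, the single value 100 would be eligible, would meet the withdrawal rule and would fail the start rule.

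**The case against.** The strongest reply is that nobody would be misled. The item's heading, the upper limits on either side, the dosing tables and the exclusion for severe liver damage all show what was meant. Section 5 ends with a machine-translation notice, so the slip may exist only in this English text and not in the protocol or form that staff used. Every dose, including the first, is still subject to the below-100 rule. No endpoint or analysis depends on the criterion. AST and ALT are required case-report entries (section 4(3)3)) and clinical testing is required at registration (section 4(3)9)), so the values applied in practice can be recovered.

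Most of this stands. The direct safety risk is limited, the effect on actual enrolment is unknown, and its practical consequences depend on whether the original-language text and the form carry the slip. Neither is shown. Nor is anything irrecoverably lost, since baseline values should be on file.

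Two points remain. The text as printed is wrong and uncorrected. The intended limit also cannot be read off with certainty: it could be < 100, ≦ 100 or another figure, because the entry limits for WBC, neutrophils and bilirubin differ from their dosing limits. The discretion in section 4(2)7) for patients whose baseline is close to a limit does not settle it, because it concerns only whether to stop during treatment.

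**Conclusion.** The concern holds. Line 5(6) contradicts the protocol's own withdrawal and start rules: the entry range for AST and ALT coincides with the withdrawal range and excludes every value at which nivolumab may be started. The other six laboratory items show no such conflict. A slip in typing or translation is by far the likeliest cause, but the document cannot prove it.

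This is a certain error in an eligibility limit that staff must confirm. It should be fixed, but it is not a threat to the trial's analysis. The number of patients affected cannot be determined. The 42-day window assumes that registration and enrolment completion coincide.

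**What to change.** - Change 5(6) to AST and ALT < 100 IU/L, in line with section 4(2)8), after clinical confirmation that this is the intended limit. Prefer < to ≦, so that a value of exactly 100 is not both eligible and at the withdrawal limit.
- Check the original-language protocol and the Enrollment Eligibility Confirmation Form, and correct them if they carry the same sign.
- For patients already registered, use the baseline AST and ALT on file to record which limit was applied, and note any patient with a value of 100 IU/L or more at registration.

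The cost is a one-character correction in the protocol (and in the form if needed) plus a look-up of values already collected. No new patient procedures are required.

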Patients with a history of hypersensitivity to any of the ingredients in this product

[Careful with doses]

1) Patients with concomitant autoimmune disease or a history of chronic or recurrent autoimmune disease [autoimmune disease may be aggravated].

2) Patients with interstitial lung disease or a history of interstitial lung disease [there is a risk of worsening of interstitial lung disease].

Serious side effects.

1) Interstitial pulmonary disease.

Since interstitial lung disease (3.6%) such as pulmonary inflammation, pulmonary infiltration, and pulmonary disorder may occur, clinical symptoms such as cough, dyspnea, fever, and abnormal lung sounds (hair twirling sound) should be carefully monitored, and if any abnormality is observed, chest X-ray, chest CT, and serum markers, etc. should be conducted promptly. If interstitial lung disease is suspected, the administration should be discontinued, and appropriate measures such as the administration of corticosteroids should be taken.

2) Myasthenia gravis, myocarditis, myositis, and rhabdomyolysis

Myasthenia gravis (frequency unknown*), myocarditis (frequency unknown*), myositis (0.1%), and rhabdomyolysis (frequency unknown*) may occur, and some cases have been further complicated by these conditions. Muscle weakness, ptosis, dyspnea, dysphagia, elevated CK (CPK), ECG abnormality, and elevated blood and urinary myoglobin should be carefully monitored. If any abnormality is observed, the administration should be discontinued, and appropriate measures such as the administration of corticosteroids should be taken. As respiratory failure may progress rapidly due to myasthenia gravis, precautions should be taken to ensure that the patient's respiratory condition does not worsen; hepatic dysfunction and jaundice with increases in AST (GOT), ALT (GPT), and γ-GTP may occur, and if any abnormalities are observed, the patient should be carefully monitored. The administration should be discontinued, and appropriate measures taken.

3) Colitis, severe diarrhea

As colitis (0.9%) and severe diarrhea (0.7%) may occur, patients should be carefully monitored.

4) Type 1 diabetes mellitus

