12) Severe skin disorders

Severe skin disorders, such as toxic epidermal necrolysis (TEN), Stevens-Johnson syndrome (Stevens-Johnson syndrome) (incidence unknown*) and erythema multiforme (0.3%) may occur; therefore, patients should be carefully monitored. In this case, drug administration should be discontinued, and appropriate measures should be taken.

13) Venous thromboembolism

As venous thromboembolism, such as deep vein thrombosis (0.1%) and pulmonary embolism (0.1%), may occur, patients should be carefully monitored, and appropriate measures such as discontinuation of administration should be taken if any abnormalities are observed.

14) Infusion reaction

Infusion reactions (2.7%), including anaphylaxis, fever, chills, pruritus, rash, hypertension, hypotension, hypotension, dyspnea, or hypersensitivity, may occur. If a severe infusion reaction is observed, the administration should be discontinued immediately, appropriate measures should be taken, and the patient should be carefully monitored until these symptoms subside.

(3) Evaluation method and endpoints

1) Primary endpoint

Overall survival time

Secondary endpoint

Progression-free survival

Response rate

Health-related quality of life scores (EORTC QLQ-C30, EORTC QLQ-H&N35)

2) Observations/examinations

Patient Background

Basic Patient Information

Date of birth, age at the time of obtaining consent (automatically calculated from the date of birth and date of obtaining consent), sex, height at the time of obtaining consent, weight at the time of obtaining consent, body surface area at the time of obtaining consent (automatically calculated from height and weight), date of obtaining written consent

Target Disease Information

Histological diagnosis: squamous cell carcinoma

Primary sites: the maxillary sinus, oral cavity, nasopharynx, nasopharynx, oropharynx, hypopharynx, larynx

Pre-treatment Stage: III, IVA, IVB, IVC

TNM Classification: T (1, 2, 3, 4a, 4b), N (0, 1, 2, 3), M (0)

3) Inspection item

The following tests and observations should be performed periodically to evaluate drug safety and disease recurrence. However, in the event of an adverse event, additional laboratory tests or observations should be performed as needed, and the patient should be monitored until laboratory values or symptoms have resolved or abated. Details on the timing of each test and observation should be in accordance with "8.2 Schedule of Tests, Observations, and Reporting".

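### Exclusion 1 is narrower than the contraindication printed in the same protocol, so a patient with an earlier non-severe reaction to nivolumab can pass the written eligibility check

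*Protocol*

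**What the plan says.** Three parts of the protocol bear on this point.

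- **Exclusion list.** Section 3(2), item 1 bars "Patients with a history of severe drug allergy of nivolumab and similar drugs".
- **Drug information.** Under the contraindication heading, section 4(2)9) has "Patients with a history of hypersensitivity to any of the ingredients in this product". The section presents itself as a summary and adds "Please refer to the most recent package insert for the drug for further information".
- **Registration.** Section 4(2)1) states "Patient enrollment will be determined by the principal investigator and sub-investigators". Section 4(2)2) gives the check: "Confirm that eligible patients meet all eligibility criteria and none of the exclusion criteria, complete the Enrollment Eligibility Confirmation Form". The principal investigator then reviews the form and issues a registration number. Under section 4(2)3), protocol treatment starts within 4 weeks.

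**The concern.** The exclusion and the contraindication address the same hazard but draw the line in different places. The exclusion has a severity threshold and the contraindication has none. The exclusion names nivolumab and similar drugs, whereas the contraindication covers every ingredient of the product. Registration is tested against the lists in section 3, so it is the narrower wording that decides who is registered.

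The narrowing also looks unintended. Section 4(2)9) places autoimmune disease and interstitial lung disease in a cautionary tier below contraindication. Section 3(2) nevertheless makes autoimmune disease (item 4) and interstitial pneumonia or pulmonary fibrosis (item 7) full exclusions. Two precautions were thus turned into exclusions while the one contraindication was limited to severe cases, and no reason is given.

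What is at stake is a small matter of patient safety and of clean registration. It is not a matter of inference.

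**Working it through.** The protocol gives no figure to reproduce, so the check is a comparison of texts.

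**Step 1: scope of the two rules.**

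| | Exclusion 1, section 3(2) | Contraindication, section 4(2)9) |
| --- | --- | --- |
| Severity | severe only | any |
| Agent | nivolumab and similar drugs | any ingredient of the product |

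Exclusion 1 is wider in one respect, since it reaches similar drugs. That does not help a patient whose earlier non-severe reaction was to nivolumab itself. The difference in agent is weaker. Section 4(2)9) gives nivolumab as the generic name and Opdivo as the product, so an allergy to nivolumab may fairly be read as an allergy to the product. The severity difference carries the point.

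**Step 2: does another written rule close the gap at registration?**

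- Inclusion items 1 to 6 and exclusion items 2 to 13 do not mention allergy, hypersensitivity or contraindications.
- Exclusion 14 leaves a judgement to the attending physician, but about physical condition.
- The check at treatment initiation in section 4(2)6) concerns laboratory values: "treatment should be continued after confirming that various laboratory tests have met the dosage criteria".
- The discontinuation rule in section 4(2)5) acts only after a reaction on treatment.
- The eligibility item among the monitoring items in section 21 adds no criterion.

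None of these makes the patient in step 1 fail the written check.

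**Step 3: what should stop dosing after registration?**

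- The contraindication is itself part of the protocol, and the package insert is referred to.
- Section 6(3)1) limits adherence to the protocol to what patient safety allows.
- Section 11 describes the treatment as part of ordinary medical care.

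Together these should prevent the infusion. What they do not undo is the registration.

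**Step 4: how many patients?** The documents do not give the share of patients with earlier nivolumab exposure, or the rate of non-severe hypersensitivity on it. No criterion bars earlier exposure. Section 1 dates insurance approval for this disease to 24 March 2017, about seven months before the protocol date of 31 October 2017, so little exposure would be expected when enrolment began.

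The following only illustrates the order of magnitude:

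- N = 50, the planned number in section 3.
- r = 2.7%, from section 4(2)9), item 14: "Infusion reactions (2.7%), including anaphylaxis, fever, chills, pruritus, rash". This is a crude proxy. It includes severe reactions, which exclusion 1 already bars, and reactions that need not be hypersensitivity.
- p = share previously exposed, assumed to be 0 to 10%, with no source in the documents.

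Expected number = N × p × r.

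- p = 0: 50 × 0 × 0.027 = 0
- p = 10%: 50 × 0.10 × 0.027 = 0.135
- p = 100%, a ceiling that nothing in the protocol suggests: 50 × 1 × 0.027 = 1.35

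A reaction to another ingredient would not need earlier nivolumab exposure, but the documents list no other ingredient, so that part cannot be sized at all.

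**The case against.** The strongest reply is that the two texts do not conflict. A contraindication bars dosing whether or not the exclusion list repeats it, and not being excluded is not permission to treat. A reader might infer from exclusion 1 that the protocol allows contraindicated patients to be dosed, or that only a physician's memory of the drug information prevents it. The documents do not support that reading, because the safeguards in step 3 are written and point the same way. This part of the reply stands, and it reduces the point to registration.

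The second reply is that *severe* may be an artefact of translation. Section 5 carries a machine-translation note, the English is uneven elsewhere, and the severity difference rests on one adjective. This also stands as a caution. It cannot be settled without the source text, so the fix starts there.

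The third reply is that the effect is nearly nil and the prior-exposure range has no source. That is correct and limits the grade. It does not make the patient in step 1 fail the written check. Nor can the matter be left to a statistical analysis plan, since eligibility belongs in the protocol.

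**Conclusion.** The point holds as a minor patient-safety correction. As written, exclusion 1 is narrower than the contraindication that the protocol prints, mainly through the severity threshold. A patient with an earlier non-severe hypersensitivity reaction to the product can pass the eligibility check and be scheduled for treatment. The likely consequence is a patient registered who should not be and who is then not dosed.

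The number affected is close to zero and cannot be sized from the documents. The figures in step 4 rest on an assumed exposure share and a rough proxy, and should not be read as an estimate. No endpoint, analysis or sample size depends on the point. The conclusion assumes that the English text reproduces the source wording and that the eligibility form, which is not shown, follows the list in section 3.

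**What to change.** First check the original-language wording of exclusion 1. If it has no severity threshold, correct the translation. If it does, reword item 1 as: *history of hypersensitivity to any ingredient of nivolumab (Opdivo), or of severe allergy to similar drugs*. Make the Enrollment Eligibility Confirmation Form match.

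The cost is one line of protocol text and a check of one form, with at most an occasional patient fewer. The supplementary quality-of-life table already reports on-treatment results, so for patients already treated the action is a look back through the eligibility records.

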**Supplementary** **Information**

**Study Protocol**

**A single-center prospective study on the efficacy of nivolumab against platinum-sensitive recurrent or metastatic head and neck squamous cell carcinoma**

1st edition

Date of completion: 31 October 2017

1. Background

A combination of surgery, radiation, and chemotherapy is the preferred treatment for advanced head and neck cancer. Patients with unresectable recurrent or metastatic squamous cell carcinoma of the head and neck (R/M-SCCHN) have a poor prognosis and usually have a life expectancy of approximately one year. FP (5FU, CDDP) is the recommended treatment for this condition, but its poor efficacy and toxicity have made long-term treatment difficult. In the EXTREME study, cetuximab was combined with cisplatin or carboplatin and FP (FPE). A high response rate of 36% was observed for the combination compared to 20% for FP alone. In the case of FPE, up to 6 cycles are provided, but in some cases, only 2 or 3 cycles are administered in practice due to adverse events. After that, cetuximab can be administered weekly until progressive disease (PD) or until the manifestation of unacceptable adverse events. Thus, instances of long-term survival of more than two to three years, which was previously unthinkable, have increased, and a regimen that includes cetuximab has become the current standard of care.

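### Single-arm efficacy study with overall survival as primary endpoint, but no survival reference, precision goal or success criterion, and a sample size justified by an accrual estimate that does not reproduce

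*Protocol*

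**What the plan says.** The title is "A single-center prospective study on the efficacy of nivolumab against platinum-sensitive recurrent or metastatic head and neck squamous cell carcinoma". Section 2 (Objectives) reads, but for its last word, "The purpose of this study is to evaluate the effects of nivolumab in patients with relapse or metastases 6 months after the completion of platinum-based". It names no hypothesis, comparator or threshold.

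Section 3 gives "Expected number of patients: 50". Section 3(3), on the evidence for the number of cases, opens with "This study is a single-arm phase II trial" and then offers accrual alone: about 4 cases a month at the centre, 30% to 40% of them eligible, two years of enrolment, and so close to 50 patients.

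Section 4(3)1) gives the primary endpoint as "Overall survival time", with no landmark or summary measure. Progression-free survival, response rate and quality of life are secondary. Section 4(3)8) ties the final survival check to one year after the last of 50 enrolments and adds an interim analysis at 20 patients, without a rule. The termination criteria in section 15(8) concern safety only.

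The one survival-like figure is in section 1: patients with unresectable recurrent or metastatic disease "usually have a life expectancy of approximately one year".

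Under Target Disease Information in section 4(3)2), one line reads "Pre-treatment Stage: III, IVA, IVB, IVC". The next reads "TNM Classification: T (1, 2, 3, 4a, 4b), N (0, 1, 2, 3), M (0", and its M list closes after that single value.

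**The concern.** Survival time in one arm shows a drug effect only when set against something external. The protocol names nothing to set it against and no result that would count as success or failure. Almost any survival curve could then be called favourable or unfavourable once seen.

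The likeliest comparison after the fact is with the one-year figure in the background section. That figure describes recurrent or metastatic disease in general. This trial takes patients whose disease appears six months after platinum, aged 20 to 75, with performance status 0 or 1 and adequate organ function. The protocol itself treats progression before and after six months as separate evidence settings, and it reports that survival beyond two to three years has become more frequent under cetuximab-containing regimens. A comparison with one year could therefore credit patient selection to nivolumab.

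Nor does the number of patients supply a standard. It follows from no error rate, target or interval width, and the feasibility estimate behind it does not give the number stated.

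**Working it through.** **1. The plan's own figure.** Inputs from section 3(3): 4 cases a month, 24 months, 30% to 40% eligible. N = rate × months × eligible share.

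- Cases seen: 4 × 24 = 96.
- At 30%: 96 × 0.30 = 28.8. At 35%: 33.6. At 40%: 38.4.
- Counting about 26 months from the protocol date (31 October 2017) to the end of enrolment (31 December 2019): 4 × 26 = 104 cases, giving 31.2 to 41.6.

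The stated figure of about 50 is not reproduced. Reaching 50 in 24 months needs 50/96 = 52% eligible, or 5.2 to 6.9 cases a month at 40% to 30% eligible. At 4 cases a month it needs 50/(4 × 0.40) = 31 to 50/(4 × 0.30) = 42 months.

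**2. Precision at these sizes.** Exact (Clopper-Pearson) 95% intervals when about half the patients are alive at 12 months:

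| N | Alive at 12 months | 95% CI |
|---|---|---|
| 29 | 14 | 29.4% to 67.5% |
| 38 | 19 | 33.4% to 66.6% |
| 50 | 25 | 35.5% to 64.5% |

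**3. What a rule could show.** The protocol gives no reference, so every reference here is an assumption. The rule is to claim activity if the lower limit of the exact two-sided 95% CI exceeds p0. Equivalently, k is the smallest count with P(X ≥ k | N, p0) ≤ 0.025, and power is P(X ≥ k | N, p1). All patients are taken as followed for 12 months.

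At p0 = 50%:

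| N | k | Observed rate needed | Power, true 65% | Power, true 70% |
|---|---|---|---|---|
| 29 | 21 | 72% | 27% | 48% |
| 38 | 26 | 68% | 40% | 66% |
| 50 | 33 | 66% | 51% | 78% |

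At N = 50 and a true rate of 65%, varying the reference:

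| p0 | k | Power |
|---|---|---|
| 37% | 26 | 98% |
| 40% | 28 | 93% |
| 50% | 33 | 51% |
| 60% | 38 | 7% |

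The background figure does not settle p0 even for the general population. Read as a median, one year means 50% alive at 12 months. Read as the mean of an exponential distribution, it means exp(−1) = 37%.

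**4. The staging lists side by side.** The stage list includes IVC, the stage group for distant metastasis, while the M list beside it offers only 0. Eligibility includes metastatic disease. The text does not say whether these fields describe first diagnosis or trial entry.

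**The case against.** The strongest reply is that the summary measure and the interval rule commonly belong in an SAP, which is not at hand, and that a small part of the protocol is also not shown. This stands to a degree: the absence is established only for the text shown. It does not cover section 3(3), which is the protocol's own place for justifying the number of cases and holds accrual alone.

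A second reply is that the objective is only to evaluate effects, and that a survival estimate with its interval, progression-free survival, response rate and quality of life all bear on that. Response can be read without a concurrent control, and the background section gives 36% and 20% for the standard regimens. This also stands. A reader might infer that the trial's data cannot address efficacy at all, but the documents do not support that. What is missing is narrower: a criterion stated in advance for concluding efficacy from the primary endpoint.

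A reader might also infer from the M list that metastatic disease cannot be recorded, and that this undermines the survival analysis. Neither follows. Stage IVC records distant metastasis indirectly, the fields may refer to initial staging, and a baseline code list does not stop survival from being estimated or tested. Primary site, T, N, stage, performance status, PD-L1 and imaging are also collected.

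**Conclusion.** The point holds in a limited form. In the text shown, a single-arm study presented as one of efficacy has survival as its primary endpoint and no reference, precision goal or success criterion, so an efficacy conclusion from survival has no pre-stated basis. The general one-year figure cannot fill the gap, because these patients are selected differently.

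The accrual shortfall needs no assumption: 29 to 38 patients over the stated two years, at most about 42 over 26 months, against a final analysis tied to 50. The power figures do rest on assumptions: an assumed reference, complete 12-month follow-up, and a binomial calculation standing in for Kaplan-Meier. Their range, 98% to 7% at N = 50 as the reference moves from 37% to 60%, shows that the missing reference decides what the trial can conclude.

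The mismatch between M (0) and stage IVC is a separate, minor data-field inconsistency and carries no weight in this conclusion.

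**What to change.** - Make the 12-month overall survival rate (Kaplan-Meier, 95% CI) the primary measure and report it descriptively, without an efficacy claim.
- The exception is a reference for comparable platinum-sensitive patients that is fixed and justified before the data are seen. In that case, claim activity only if the lower confidence limit exceeds it. Do not use the general one-year figure as the threshold: acknowledging its selection bias would not remove it.
- State the operating characteristics over a range of references, labelled as assumptions, for 50 patients and for the 29 to 38 that the accrual inputs support.
- Reconcile the stated number with those inputs: correct the case rate, eligible share or enrolment period, or lower the number and the trigger for the final analysis.
- Separately, change the M list to 0 and 1, say whether staging is at first diagnosis or at entry, and record local recurrence versus distant metastasis at entry.

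The cost is protocol wording and a small change to the case report form. Survival of all patients is already to be checked one year after the last enrolment, so no further follow-up is needed. The downside is that a positive claim becomes harder to make.
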